### Recruitment {15}

Participants will be recruited by participating GPs or specialists (neurologists, psychiatrists) practices in the participating physician’s networks. To identify community-dwelling patients, GPs approach their patients who already have received a formal dementia diagnosis and systematically screen patients at 70 and above for dementia using the DemTect instrument [48]. People who meet all inclusion criteria will be informed by their GP in detail about the study and invited to participate. Patients who provide written IC to participate will subsequently be included in the study.

## Assignment of interventions: allocation

### Sequence generation {16a}

Five physician networks participate in the study. In each network, participating practices are randomized following a 1:2-format to either the intervention- or waiting-control group. Block randomization will be computer-generated and operated in blocks size six using RandList software (Version 2, Datinf, Germany).

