### Concealment mechanism {16b}

The allocation list is concealed by access restrictions. Only staff of the project evaluation team has access to the allocation list. Non-authorized staff cannot access the allocation list.

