### Implementation {16c}

GPs were allocated based on a 1:2 (intervention:waiting list) cluster-level block randomization. The assignment list at the cluster level with defined assignments to the groups was determined prior to physicians’ assignment. The assignment of GPs was implemented when the first patient provided written informed consent in a GP practice. Physicians, therefore, filled in the next available slot on the assignment list, either the waiting list or the intervention group, when the study center received the informed consent documents. Thus, physicians’ participation decisions were made independently and prior to their group assignment.

The allocation sequence will be performed by the evaluation team using RandList software.

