## Assignment of interventions: blinding

### Who will be blinded {17a}

Due to the nature of the intervention in this study, it is not possible to blind the study staff (nurses or practitioners) or the participants. Physicians and patients will become aware of their randomization status throughout the course of the study. The study is not blinded.

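### One fixed block size of six, filled in order of first consent in an unblinded trial, leaves up to about 28% of practice allocations deducible in advance by a fully informed observer, so restricting access to the list does not fully secure concealment

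*Protocol article*

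**What the plan says.** All references are to the protocol article.

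- **Sequence generation {16a}:** "Five physician networks participate in the study", and in each of them "participating practices are randomized following a 1:2-format to either the intervention- or waiting-control group". The method is: "Block randomization will be computer-generated and operated in blocks size six using RandList software". No variation in block size is mentioned.
- **Implementation {16c}:** the list is prepared in advance. "The assignment of GPs was implemented when the first patient provided written informed consent in a GP practice". Physicians then "filled in the next available slot on the assignment list, either the waiting list or the intervention group", once the consent documents had reached the study centre. The section concludes that the decision to take part was independent of the assignment and came before it.
- **Concealment mechanism {16b}:** "The allocation list is concealed by access restrictions", and only the evaluation team may see it.
- **Who will be blinded {17a}:** "The study is not blinded".
- **Sample size {14}:** 93 practices, of which 31 are intervention and 62 waiting-control.

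**The concern.** Concealment needs more than a hidden list: the next allocation must also be impossible to work out from those already made. With a single block size and visible arms, whoever keeps a tally can sometimes do so. Once a block has used both intervention slots, all its remaining slots are waiting-control. Once it has used all four control slots, the rest are intervention.

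Arms are visible in practice. Under Plans for assessment {18a}, baseline visits are made by study nurses in control practices and by dementia specialised nurses in intervention practices. Under Confidentiality {27}, both groups can review the GPs in their own region. The study centre receives the document that triggers allocation. Regional nurses and study-centre staff are therefore more plausible observers than a single GP, who by the text sees only the practice's own arm.

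The slot depends on when one document arrives, so an informed person who handles or prompts that document could influence the arm. At stake is the practice-level comparability on which the whole comparison rests, and with it the independence claimed under Implementation {16c}.

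**Working it through.** **Inputs.** Block size 6, ratio 1:2 and five networks (Sequence generation {16a}); 93 practices (Sample size {14}). The article gives no predictability figure to reproduce. Its split does reproduce: 93 × 1/3 = 31 and 93 × 2/3 = 62.

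**Orders in a block.** Two intervention and four control slots can be ordered in C(6,2) = 15 equally likely ways. A slot is certain when one arm is already used up in its block. *Optimal guess* means naming the arm with more slots left.

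| Position in block | P(slot certain) | P(optimal guess right) |
|---|---|---|
| 1 | 0 | 10/15 |
| 2 | 0 | 10/15 |
| 3 | 1/15 | 10/15 |
| 4 | 3/15 | 11/15 |
| 5 | 7/15 | 11/15 |
| 6 | 15/15 | 15/15 |
| Sum | 26/15 = 1.733 | 67/15 = 4.467 |

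**Certain slots, complete blocks.** 1.733 / 6 = 28.9%. The closed form agrees: 4/(2+1) + 2/(4+1) = 1.333 control + 0.400 intervention = 1.733. So 1.333/1.733 = 77% of certain slots are control, and known intervention slots are only 0.400/6 = 6.7% of all slots.

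**Guessing.** 4.467 / 6 = 74.4%, against 4/6 = 66.7% for always guessing control.

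**At 93 practices, with incomplete last blocks:**
- One list: 15 blocks × 26/15 = 26, plus 1/15 for the three further slots, gives 26.07; 26.07/93 = 28.0%.
- Five near-equal networks (18, 18, 19, 19, 19): 15 complete blocks, and the three leftover first slots add nothing; 26/93 = 28.0%.
- Lowest split with at least 3 practices per network (4, 4, 4, 4, 77): 4 × 4/15 = 1.07, plus 12 × 26/15 = 20.8, plus 11/15 = 0.73, gives 22.6; 22.6/93 = 24.3%.

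The article does not give the network sizes, so the range is 24% to 28%. It is not entirely clear whether there is one list per network or a single list; the percentage hardly changes.

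**Alternatives.** A fixed block of 3 gives 44.4% certain slots, of 9 gives 21.4% and of 12 gives 17.0%. For varying blocks I computed the optimal guess over 18 practices (93/5 = 18.6 per network). Sizes are equally likely, and the observer knows the set of sizes but not their order.

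| Scheme | Certain slots | Optimal guess right |
|---|---|---|
| Fixed 6 | 28.9% | 74.4% |
| Varying 3, 6, 9 | about 3% | about 73% |
| Varying 6, 9, 12 | about 2% | about 71% |

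**The case against.** The strongest reply is that 28% is a ceiling. It needs someone who knows the block size, the block boundaries and every earlier allocation in the network, and the article shows nobody with all three who also controls when a first consent arrives. Regional access to GP records does not by itself reveal the order of allocation or where a block starts. The evaluation team that holds the list is described as independent of the consortium leader. All this stands, and the figure must be given as conditional.

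The practical gain is also modest. Complete knowledge lifts guessing success by less than 8 percentage points (74.4% against 66.7%). Because few certain slots are intervention, someone who wants that arm could mostly only hold back until others had filled the control slots. Waiting-control practices receive the intervention after 6 months, which weakens the motive. These points limit the size of the problem but do not remove it.

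A reader might infer that practices did time their entry, or that they could read the block size in print while recruiting. The article supports neither. It describes no steering of entry, and its publication date is not shown. Nor is the statement that the participation decision came before assignment contradicted: the consent trigger does put the decision first. What the design does not secure is the other half of that statement, independence, because this also requires that the coming slot cannot be foreseen.

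**Conclusion.** The concern holds as a limited weakness of concealment, not as a demonstrated bias. With one fixed block size, sequential filling and visible arms, restricted access to the list does not fully prevent prediction. For an observer with full knowledge, up to about 28% of practice allocations (about 26 of 93, roughly three quarters of them waiting-control) are certain beforehand, or 24% to 28% depending on network sizes, and optimal guessing succeeds 74% of the time against 67%.

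This rests on two assumptions: the block size is a constant six, as the text reads, and the observer knows it together with the block boundaries and all earlier allocations in the network. With less knowledge, predictability is lower. It would be wrong to conclude that practice-level balance has been lost: that would follow only if someone had used the foreknowledge, and nothing in the article shows it. The change is worth making because it is cheap and concerns the randomisation itself.

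**What to change.** **Practices not yet allocated.** Regenerate the unused part of each network's list with randomly varying block sizes that keep 1:2, for example 6, 9 and 12. Leave out 3, the most predictable size. The sizes should be known only to the evaluation team and not disclosed until recruitment ends. The main gain is in certain slots (about 29% to about 2%); overall guessing success falls only from about 74% to about 71%. Alternatively, allocate ready practices in batches per network, so that no single practice's timing picks its slot.

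**Practices already allocated.** Implementation {16c} is written in the past tense. The article is protocol version 2.0 of 2 May 2021, with enrolment running from January 2021 to an estimated end in June 2022, so some or all practices may already have an arm. For these, report allocation order and consent receipt dates by network, so that readers can look for signs of steered entry.

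**Cost.** One regeneration of the unused list, and a network may end slightly further from exact 1:2. If allocation is complete, only the reporting step remains.

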### Concealment mechanism {16b}

The allocation list is concealed by access restrictions. Only staff of the project evaluation team has access to the allocation list. Non-authorized staff cannot access the allocation list.

### Implementation {16c}

GPs were allocated based on a 1:2 (intervention:waiting list) cluster-level block randomization. The assignment list at the cluster level with defined assignments to the groups was determined prior to physicians’ assignment. The assignment of GPs was implemented when the first patient provided written informed consent in a GP practice. Physicians, therefore, filled in the next available slot on the assignment list, either the waiting list or the intervention group, when the study center received the informed consent documents. Thus, physicians’ participation decisions were made independently and prior to their group assignment.

The allocation sequence will be performed by the evaluation team using RandList software.

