### Sample size {14}

The primary endpoint of this study is the number of unmet needs. Recent literature points out that PwDs have on average 1.87 unmet needs with a standard deviation of 2.0 [47]. The sample size calculation was based on an assumed reduction of the number of unmet needs of 35% and a randomization ratio of 1:2 (1: intervention group, 2: waiting list). In a previous study, where dementia care management was also carried out, and patients were recruited from GP practices, there was an intra-cluster correlation (ICC) of 0.16 with a variance of ICC of 0.06 and a cluster size of five (five patients per GP practice). This ICC, variance of ICC, and cluster size were also used to calculate the sample size for this study. Therefore, a sample size of *n* = 345 PwD and 69 clusters would be needed to demonstrate an implicit effect of 1.22 unmet needs in the intervention group compared to 1.87 unmet needs in the control group at a significance level of *α* = 0.05 and statistical power of 80%. A loss to follow-up of about 30% was assumed due to the elderly population and the inclusion of a waiting-list group. Overall, this requires the recruitment of *n*=465 participants of 93 clusters to demonstrate a significant intervention effect. Therefore, a total of *n* = 310 patients in the waiting-control group (recruited from 62 GP practices) and *n* = 155 patients in the intervention group (from 31 GP practices) will be necessary to detect a significant difference between the intervention and the waiting control group concerning a 35% reduction of unmet care needs.

The randomization ratio of 1:2 was used due to the higher probability of dropouts in the waiting control group, which is predominantly a problem in times of the COVID-19 pandemic and the introduced lockdowns, contact restriction and the high risk of severe COVID-19 progressions, subsequent hospitalization, and death in the elderly population.

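### Allocating a practice at its first patient's consent lets an unblinded GP choose most later patients with the arm knowable: up to 372 of 465 (80%), fewer if several consents arrive first

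*Protocol article*

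**What the plan says.** Under Implementation {16c}, the assignment list exists before any practice is placed on it, and the trigger for placement is patient consent: "The assignment of GPs was implemented when the first patient provided written informed consent in a GP practice". The practice takes the next slot "when the study center received the informed consent documents". From this order the article concludes that physicians' "participation decisions were made independently and prior to their group assignment".

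Recruitment {15} gives patient selection to the GP, who approaches patients with a diagnosis and screens others aged 70 and over. It continues: "People who meet all inclusion criteria will be informed by their GP in detail about the study and invited to participate". The section on who takes consent {26a} makes the GP responsible for verifying capacity to consent.

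The section on blinding {17a} states that the study is not blinded and adds: "Physicians and patients will become aware of their randomization status throughout the course of the study". Concealment {16b} restricts access to the list and says nothing about a practice's arm once assigned. Under the plans for outcome assessment {18a}, the baseline visit is made by study nurses in the control arm and by dementia-specialised nurses in the intervention arm.

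Sample size {14} plans "a cluster size of five (five patients per GP practice") and the "recruitment of *n*=465 participants of 93 clusters". Enrolment runs from 1 January 2021 to the end of June 2022 (Trial status).

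**The concern.** In a cluster trial, randomisation protects the comparison of patients only if patients are identified before allocation, or by someone who does not know the arm. Here the order protects the recruitment of practices. Every patient after the first can be approached, judged capable and invited by a GP who may know whether the nurse comes now or in 6 months. Patients and caregivers may know it too when they decide.

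If recruitment then differed between arms, the case mix would differ, and so could the number of unmet needs before any intervention effect. It could go either way: GPs with immediate nurse support might put forward patients with more needs, or waiting-list GPs might invite fewer or easier ones. Caregiver participation could shift as well, and it decides which CANE version is used (Outcomes {12}). Intention-to-treat analysis and multilevel models do not help, because they take the enrolled patients as given.

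**Working it through.** **1. Cluster size (Sample size {14}).** The article's figures agree with one another: 465/93 = 5, 345/69 = 5, 310/62 = 5 for the "patients in the waiting-control group (recruited from 62 GP practices"), and 155/31 = 5 for the intervention arm.

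**2. Share recruited after the arm is knowable.** If k consents per practice arrive before the arm can be known, the exposed share is (465 − 93k)/465 = 1 − k/5.

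| k (assumed) | Exposed patients | Share |
|---|---|---|
| 1 | 465 − 93 = 372 | 80% |
| 2 | 465 − 186 = 279 | 60% |
| 3 | 465 − 279 = 186 | 40% |

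At k = 1 this is 155 − 31 = 124 intervention patients and 310 − 62 = 248 control patients, the same share in each arm. The row k = 1 is the literal reading of the trigger. Rows 2 and 3 allow for several forms sent together, or for consents obtained before the practice learns its arm.

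The share also moves with actual cluster size. With one consent first it is 1 − 1/m, which is 67%, 75%, 83% and 88% for m = 3, 4, 6 and 8.

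**3. Would the planned baseline check catch it?** Statistical methods {20a} compares the arms at baseline and adjusts if significant differences appear. Inputs from Sample size {14}: SD 2.0, ICC 0.16, five per practice, 155 versus 310 patients. Assumptions: the SD and ICC apply to baseline unmet needs, and the test is two-sided at 0.05.

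- Design effect = 1 + (5 − 1) × 0.16 = 1.64.
- SE of the difference = 2.0 × √[1.64 × (1/155 + 1/310)] = 0.252.
- Chance of a significant result is approximately Φ(d/0.252 − 1.96).

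| True baseline imbalance d (illustrative) | d/SE | Chance of being flagged |
|---|---|---|
| 0.2 needs | 0.79 | about 12% |
| 0.4 needs | 1.59 | about 35% |
| 0.65 needs (1.87 − 1.22, the whole target effect) | 2.58 | about 73% |

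These values of d show how sensitive the check is. They are not estimates of bias in this trial. Because the baseline assessor differs by arm, a flagged difference could also reflect who did the assessment.

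**4. What could an analysis limited to patients consented before release show?** At k = 1 it has about 31 versus 62 patients, one per practice, so within-practice clustering does not enter. SE = 2.0 × √(1/31 + 1/62) = 0.440, and 0.65/0.440 = 1.48. Power is therefore about 32% before any dropout, too low to confirm or rule out bias.

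**The case against.** The strongest reply is that the article's conclusion in {16c} is true as written. It speaks only of physicians' participation, which did precede assignment, and it makes no claim about patient selection. That stands: this is a weakness of a design choice, not a false statement.

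The 80% is also a ceiling. Release follows receipt of documents at the study centre, several consents may arrive together, and the article says only that the arm becomes known during the study. The exact moment of disclosure may be left to the full protocol. This stands too, and is why the range is given.

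There are partial safeguards. Eligibility rests on age and on a DemTect threshold or a formal diagnosis, GPs are to screen systematically, controls receive the same care after 6 months, and baseline differences are to be checked. These narrow the GP's discretion and incentive but do not remove them. Step 3 shows how little the check would catch, and it cannot see unmeasured differences.

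A reader might infer that case mix did shift between arms, or that a definite fraction of the 0.65 target effect is bias. The document does not support this. It contains nothing on how selection differed, in which direction or by how much, and nothing shows that caregiver participation depended on knowing the arm.

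**Conclusion.** The point holds as an unprotected opportunity for differential recruitment. Up to 80% of patients (372 of 465) can be selected by an unblinded GP once the practice's arm is knowable. The figure is 60% or 40% if two or three consents precede that knowledge. It rests on the planned five patients per practice and on the literal trigger of one consent. No section says that all of a practice's patients are identified before allocation, or that someone unaware of the arm recruits the later ones.

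The assurance in {16c} does not reach this risk, and the significance-triggered adjustment in {20a} is a weak remedy. Occurrence, direction and size of any bias cannot be derived from the document. The correction is nevertheless worth making, because it is cheap and protects the primary comparison.

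**What to change.** **Practices not yet allocated.** Release the slot only when the practice has sent its list of consented patients, or at a fixed cut-off after its first consent, whichever comes first. Flag patients added later. The length of the cut-off is for the trial team to choose.

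**All practices, including those already allocated.**
- Record each patient's consent date against the date the practice's allocation was released.
- Pre-specify adjustment of the primary model for baseline CANE unmet needs, whatever the baseline test shows. This uses all patients.
- Report baseline characteristics and caregiver participation by arm, separately for patients consented before and after release. A difference between arms that appears only after release would point to selection.
- Present the analysis restricted to patients consented before release (about 31 versus 62) only as a descriptive check of consistency.

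**Cost.** One study-centre procedure, two dates per patient, one covariate and one table. First patients in a practice wait some weeks for allocation and a few may be lost meanwhile, which matters in a trial that already assumes about 30% loss to follow-up. Enrolment had begun before this protocol version, so the procedural change reaches only the remaining practices. Adjustment for baseline CANE handles only what that score measures, and the baseline assessor still differs by arm.

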## Assignment of interventions: blinding

### Who will be blinded {17a}

Due to the nature of the intervention in this study, it is not possible to blind the study staff (nurses or practitioners) or the participants. Physicians and patients will become aware of their randomization status throughout the course of the study. The study is not blinded.

### Procedure for unblinding if needed {17b}

Not applicable.

## Data collection and management

### Plans for assessment and collection of outcomes {18a}

After study inclusion, all participants will receive a baseline assessment in their homes carried out by study nurses in the waiting-control group and dementia specialized nurses in the intervention group. Follow-up assessments will be carried out 6 months after the baseline assessment by the dementia specialized nurses in both study groups.

The primary outcome participants’ unmet needs will be assessed by using the Camberwell Assessment of Need for the Elderly (CANE). It consists of 27 categories (including two categories for the caregiver), which assess participants’ needs in various domains (e.g., living situation, household, nutrition, personal hygiene) followed by a question, whether the participant has an unmet need in this area (yes, no) [49]. CANE has been determined suitable for scientific use in dementia and demonstrates appropriate criterion validity [50]. It can easily be used by a wide range of professionals without formal training.

Secondary outcomes include (i) the Quality of Life in Alzheimer’s Disease (Qol-AD), a 13-item questionnaire designed to provide both a patient and a caregiver report of the quality of life. Each QoL-AD item is rated on a four-point scale, ranging from poor (1) to excellent (4). Results of the Qol-AD can be summarized in a score ranging from 13 to 52, in which higher numbers indicate higher quality of life [51]. (ii) Caregiver burden will be assessed by using the Zarit Burden Inventory, a caregiver self-report 22-item questionnaire. Each item on the interview is a statement which the caregiver is asked to rate using a 5-point scale. Response options range from 0 (never) to 4 (nearly always). The result of the instrument is a sum between 22 and 88, higher results indicate a higher subjective level of burden [43]. (iii) In addition to the quantitative analyses, we will perform qualitative interviews to assess the acceptance and satisfaction of the innovative care concept from different perspectives: people with dementia, caregivers, DCMs, and GPs. Qualitative data will be evaluated using content analyses [44]. (iv) Health economic analyses will assess the cost-effectiveness of the dementia care management compared to usual care by using the EQ-5D-5L [50], RUD (Resource Utilization in Dementia Questionnaire) [45], and FIMA (Questionnaire for Health-Related Resource Use in an Elderly Population) questionnaires [46]. The EQ-5D-5L is a standardized generic instrument for measuring health status. It has been widely used in population health surveys, clinical studies, and economic evaluation, measuring patients’ health utility in five dimensions: mobility, self-care, usual activities, pain/discomfort, and anxiety/depression. Health utilities will be combined with patients’ mortality as quality-adjusted life years by using the area under curve method. The RUD [45] and FIMA [46] instruments will be used to determine the utilization of informal care and caregivers’ productivity losses and the utilization of healthcare services from a payer’s perspective, respectively.

